## Abstract

**Background:**

The optimal level of ligation of the inferior mesenteric vein (IMV) during rectal cancer surgery remains unclear. Lymph nodes are distributed at the root of the IMV, but whether root ligation and lymphadenectomy significantly increase the number of lymph nodes harvested or improve patient prognosis remains unclear. This multicenter randomized–controlled trial was designed to compare long-term survival and short-term outcomes (surgical complications, lymph node yield, postoperative recovery) between high and low IMV ligation during laparoscopic radical rectal cancer resection.

**Methods:**

This multicenter randomized–controlled trial will enroll 1,516 patients undergoing laparoscopic-assisted radical resection for rectal cancer. Participants will be recruited and randomized (1:1) by using a dynamic minimization algorithm to balance covariates, including age, sex, American Society of Anesthesiologists classification, tumor location, body mass index, preoperative clinical stage, and neoadjuvant therapy. Patients will be allocated to either high ligation or low ligation of the IMV. The primary endpoint is 3-year disease-free survival.

**Discussion:**

The IMV ligation level is a critical yet controversial step in radical rectal cancer resection. High-level evidence is lacking regarding whether high IMV ligation improves rectal cancer prognosis, necessitating robust evidence to determine the optimal ligation level.

**Trial registration:**

ChiCTR, ChiCTR2300069149. Registered 8 March 2023, https://www.chictr.org.cn/showproj.html? proj=187562.

## Introduction

Colorectal cancer (CRC) has a high global incidence, ranking as the third-most common malignancy worldwide according to the latest World Health Organization data, with ∼915,900 deaths annually. Surgery remains the cornerstone of CRC treatment [1]. The optimal level of ligation of the inferior mesenteric vein (IMV) during rectal cancer surgery remains unclear. European and American scholars advocate high ligation at the lower pancreatic border, aligning with central vascular ligation principles to minimize tumor dissemination, enhance lymphadenectomy at the vascular root, and facilitate tension-free intestinal anastomosis [2]. Conversely, Japanese guidelines recommend caudal ligation of the IMV to mitigate intestinal congestion [3]. The classic surgical textbook Huang Jiasi Surgery, Eighth Edition recommends that the disconnected IMV should be exposed on the outside of the root of the inferior mesenteric artery [4].

NCCN guidelines recommend the surgical principle of total mesorectal excision (TME) to dissect the lymphatic drainage area of the tumor and do not recommend routine extended lymphadenectomy [5]. ESMO guidelines emphasize high-quality surgical resection (TME) [6]. The Japanese Guidelines for Diagnosis and Treatment of Colorectal Cancer (8th Edition) do not have special restrictions on the selection of rectal cancer surgery; in principle, TME is used as the benchmark and the scope of the lymphadenectomy is determined by the depth of tumor invasion and preoperative lymph node evaluation, and prophylactic extended lymphadenectomy is generally not performed [7]. The Chinese Guidelines for the Diagnosis and Treatment of Colorectal Cancer (2020 Edition) recommend the removal of lymph nodes and adipose tissue in the mesorectum and lateral lymph nodes that are suspected of being positive [8]. Neither domestic nor foreign guidelines have clarified the method of IMV ligation. It is believed that lymph nodes are distributed along arteries, and the ligation and dissection of lymph nodes at the root of the IMV have not become a standard procedure for TME surgery [9]. However, it has been shown that there is a distribution of lymph nodes in the root of the IMV, and it is unclear whether root ligation and lymphadenectomy can significantly increase the number of lymph nodes harvested and whether they can improve the prognosis of patients [10].

Studies on the effects of IMV ligation levels on short-term and long-term efficacy in patients are rare. Previous studies have reported that, compared with high ligation (at the inferior pancreatic border), surgical outcomes (operation time, intraoperative blood loss, postoperative drainage, hospital stay), oncological parameters (pathological stage, lymph node yield, positive lymph nodes), and functional follow-up scores (postoperative physical score, voiding function score, defecation function score, intestinal function score, and radiotherapy and chemotherapy side effect score) were comparable, while the time to first flatus was shorter (49.30 ± 19.88 vs 67.83 ± 23.00 h, *P *< 0.05) [11]. There is no high-quality evidence-based medical evidence to confirm whether the ligation methods at different parts of the IMV affect the long-term prognosis of patients with rectal cancer.

## Objectives

This multicenter randomized–controlled trial aims to compare long-term survival (primary) and short-term outcomes (surgical complications, lymph node yield, postoperative recovery) between high and low IMV ligation during laparoscopic radical resection for rectal cancer to determine the optimal level of IMV ligation.

## Methods and trial design

### Subjects of the study

The inclusion criteria for participants were as follows: (i) age 18–75 years; (ii) diagnosis of malignant tumors confirmed by colonoscopic pathological biopsy and indicated for laparoscopic radical resection of rectal cancer; (iii) preoperative imaging (pelvic/rectal magnetic resonance imaging [MRI] mandatory) confirming clinical stage I (T2N0M0), II (T3–4N0M0), or III (T1–4N1M0 or T1–4N2M0) on the American Joint Committee on Cancers TNM Staging System for Colorectal Cancer (Eighth edition, 2017); (iv) completion of pelvic/rectal MRI for clinical staging; (v) American Society of Anesthesiologists (ASA) Grades I–III; and (vi) willingness to participate and cooperate with the study. The exclusion criteria were as follows: (i) a history of other malignant tumors and abdominal vascular surgery; (ii) patients contraindicated for laparoscopic surgery (such as those with extensive adhesion caused by a previous major abdominal surgery or patients not suitable for pneumoperitoneum); (iii) patients with intestinal obstruction, perforation, or bleeding and other conditions requiring emergency surgery; (iv) pregnant or lactating women; or (v) patients who planned to participate in other clinical studies.

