#### Neoadjuvant therapy

Neoadjuvant chemoradiotherapy is recommended for rectal cancer <12 cm from the anus. Neoadjuvant chemoradiotherapy: Long-course chemoradiotherapy is used and a total dose of 45.0–50.4 Gy is recommended for primary tumors and high-risk areas, with 1.8–2.0 Gy each time, for a total of 25–28 cycles. During radiotherapy, 5-FU or capecitabine monotherapy is given concurrently. The specific situation of neoadjuvant therapy is as follows: (i) Direct surgery is recommended for patients with Tl–2N0M0 or for those with contraindications to radiotherapy and chemotherapy, and neoadjuvant therapy is not recommended. (ii) For patients with resectable rectal cancer with T3 and/or N^+^, preoperative neoadjuvant chemoradiotherapy is recommended in principle; neoadjuvant chemotherapy alone can also be considered after multidisciplinary treatment discussion and then combined with radiotherapy on the basis of efficacy evaluation, with preoperative chemoradiotherapy recommended for patients with stage T4 disease. (iii) For patients who are not suitable for radiotherapy, it is recommended to decide whether to undergo simple neoadjuvant chemotherapy based on multidisciplinary treatment discussions (refer to the Chinese Colorectal Cancer Diagnosis and Treatment Standards 2020).

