### Subject management

#### Subject exclusion criteria

After being selected for randomization, the patient requested to withdraw from the study because of various considerations.There are no data after entering the queue.Intraoperative findings of tumor involvement requiring multivisceral resection, distant metastasis, or inability to complete the planned laparoscopic radical resection.Other reasons need to be excluded as determined by the investigator.

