##### Dropout treatment

When subjects drop out, the investigator will contact the subjects as much as possible by visiting their homes, making appointments for follow-up, telephone, and letters, among others, asking for reasons and to complete the evaluation items that can be completed. If the experimental case is withdrawn because of adverse reactions, the investigator should take corresponding treatment measures according to the actual situation of the subject. The relevant test data of the expulsion cases are properly maintained, i.e. they are kept as documents, and they are also required for the full analysis set (FAS) statistics. Patients who have dropped out do not need to be replaced.

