#### Enrollment

All the enrolled patients should be screened in strict accordance with the inclusion criteria and the qualified research centers can conduct intraoperative randomization after intraoperative exploration and definitive radical surgical resection to minimize the rejection rate of the enrolled patients.

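### T4 tumours enter without subdivision and the need for multivisceral resection is a ground for exclusion, but the protocol does not say whether that exclusion may follow allocation

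*Protocol article*

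**What the plan says.** **Entry.** *Subjects of the study* accepts "clinical stage I (T2N0M0), II (T3–4N0M0), or III (T1–4N1M0 or T1–4N2M0". T4 appears in stages II and III without a T4a/T4b split, although the adjuvant-therapy rules do separate the two. Pelvic or rectal MRI is mandatory. The patient must be "indicated for laparoscopic radical resection of rectal cancer". None of the five entry exclusions names adjacent-organ invasion or a planned multivisceral operation. The nearest concerns "patients contraindicated for laparoscopic surgery (such as those with extensive adhesion caused by a previous major abdominal surgery or patients not suitable for pneumoperitoneum".

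**Later exclusion.** *Subject exclusion criteria*, under *Subject management*, includes "Intraoperative findings of tumor involvement requiring multivisceral resection, distant metastasis, or inability to complete the planned laparoscopic radical resection". The same list opens with "After being selected for randomization, the patient requested to withdraw from the study because of various considerations".

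**Timing.** *Enrollment*, under *Quality-control measures*, says qualified centres "can conduct intraoperative randomization after intraoperative exploration and definitive radical surgical resection to minimize the rejection rate of the enrolled patients". The section *Randomization* describes the web-system request and gives no operative time point.

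**Analysis.** *Dropout treatment* keeps the data of expelled cases and says "they are also required for the full analysis set (FAS) statistics". *Evaluation and analysis of efficacy* defines the FAS as all randomised subjects after a limited, justified removal, and also states that the ITT analysis of primary and secondary endpoints uses the whole population.

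**The concern.** The entry list and the exclusion list describe different populations. The overlap is foreseeable: the trial expects T4 disease, "with preoperative chemoradiotherapy recommended for patients with stage T4 disease", and some T4 tumours involve neighbouring organs.

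The difference is harmless if such patients are found and set aside before allocation, because they are then screen failures. It is not harmless if they can be removed afterwards. The judgement that a tumour needs multivisceral resection belongs to the surgeon, and *Blinding* states that surgeons know the allocation. The arms also differ in how far the dissection goes. Removing patients after allocation on such a judgement breaks the protection that randomisation gives, and any imbalance between arms in who is removed would pass into the DFS comparison.

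**Working it through.** The plan states no figure on this point, so the check is a comparison of sections.

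**1. Can one patient meet the entry criteria and also the exclusion item?** Yes. The T4 wording is unrestricted and no entry exclusion names organ invasion. The requirement of an indication for laparoscopic radical resection limits this only indirectly. The exclusion list itself gives multivisceral resection and failure to complete the laparoscopic operation as separate grounds, so the protocol does not treat the first as already covered by laparoscopic operability.

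**2. Does the item apply before or after allocation?** The text does not settle it.
- Pointing to after: the list stands apart from the entry exclusions, its first item is explicitly after randomisation, and inability to complete an operation may show itself only once dissection is under way.
- Pointing to before: *Enrollment* describes randomisation after exploration, with the aim of keeping rejections low. Its wording must mean once radical resection has been judged feasible, since the ligation level is part of the resection. On that route many cases would be found before allocation.
- What remains open: the verb in *Enrollment* permits and does not require. Even where it is followed, the need to resect a neighbouring organ may emerge only during dissection.

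**3. What happens in the analysis to a patient removed after allocation?** Three statements bear on this.

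| Section | Statement in substance | Direction |
|---|---|---|
| *Dropout treatment* | Expelled cases are kept and needed for the FAS | Retain |
| *Evaluation and analysis of efficacy*, ITT sentences | Changed operations go into the ITT population; whole population analysed | Retain |
| *Evaluation and analysis of efficacy*, FAS sentence | Some randomised subjects may be taken out | Permits removal |

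No sentence says which governs a patient who meets the multivisceral item. Nor is it stated that a subject removed under that list counts as an expelled case in the sense of *Dropout treatment*, which is written about dropouts. Two statisticians could build different primary populations from this text.

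**4. Does another part of the design absorb it?** Minimisation balances clinical stage as I, II or III, so it does not balance T4 tumours as such. The 20% allowance in *Number of research cases* is described as loss to follow-up. Dropouts are not replaced.

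**5. Scale.** The documents give no share of T4b tumours or of multivisceral operations. For illustration only, with an assumed share p of the 1,516 planned patients (758 per group):

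| Assumed p | 1,516 × p | 758 × p (per group) | Left of 1,516 |
|---|---|---|---|
| 2% | 30.3 | 15.2 | 1,485.7 |
| 5% | 75.8 | 37.9 | 1,440.2 |
| 10% | 151.6 | 75.8 | 1,364.4 |

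These would be removals only if every such patient were allocated before the finding and then taken out. They are ceilings under an assumption, not forecasts.

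**The case against.** The strongest reply has four parts.

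*Randomisation follows exploration.* Where that is done, a tumour seen at exploration to need multivisceral resection never reaches allocation. This stands for those cases. It does not cover centres that allocate earlier, which the wording allows, or findings made during dissection.

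*The item concerns operative findings.* Invasion already visible on the mandatory MRI is not naturally an intraoperative finding, and an imaging-based entry list may differ from an operative one without contradiction. A patient with a planned multivisceral operation arguably also fails the requirement of an indication for laparoscopic radical resection. And baseline T4 need not mean multivisceral surgery after preoperative treatment. All of this stands. A reader might infer that the trial knowingly enrols every organ-invading tumour and then discards it; the documents do not support that.

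*Removed patients stay in the analysis.* *Dropout treatment* and the ITT sentences point that way, so it would be wrong to say that the plan drops these patients from the primary analysis. But the FAS sentence leaves room to do so, and nothing resolves the conflict.

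*No bias has been shown.* This stands. Nothing in the documents links the level of venous ligation to the need for adjacent-organ resection, and removal that is equal in both arms would narrow the population without favouring either arm. The point is that the text leaves differential removal possible, not that it will occur.

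**Conclusion.** The point holds as a matter of unreconciled text. T4 is admitted without subdivision, an intraoperative exclusion item has no stated timing, randomisation after exploration is optional, and the analysis-set wording can be read either way. Together these allow removal after allocation on an unblinded judgement.

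The number of patients affected and any effect on DFS cannot be derived from the documents. The 30 to 152 patients above rest wholly on an assumed 2% to 10%. Two stronger conclusions are tempting and should not be drawn: that the exclusion is certainly applied after randomisation, and that entry must be limited to T4a. The first is contradicted by the route that *Enrollment* describes. The second is a choice of trial population, and MRI screening could not in any case remove every finding made at surgery.

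The correction is worth making because it closes a route to selection bias at almost no cost.

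**What to change.** Reconcile *Subjects of the study*, *Subject exclusion criteria*, *Enrollment*, *Dropout treatment* and *Evaluation and analysis of efficacy*:

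1. State in *Enrollment* and in *Randomization* that allocation always follows intraoperative exploration.
2. State in *Subject exclusion criteria* that the intraoperative items (multivisceral resection, distant metastasis, inability to complete the planned operation) are screen-failure criteria and apply before allocation only.
3. State that a patient found after allocation to meet one of them stays in the ITT/FAS analysis of DFS in the allocated arm, and may be left out of the per-protocol set only. The same rule should cover anyone already allocated.
4. Align the T4 entry wording with the exclusion list, using the MRI that is already required. Which T4 tumours are eligible is for the sponsor to decide.

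The cost is a few lines of amendment and no new examination. The price in the analysis is that a small number of patients who did not receive the planned operation remain in the primary comparison.

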### Number of research cases

This is a superiority trial. The 3-year disease-free survival (DFS) rates of patients with high inferior mesenteric artery (IMA) ligation were 86.1% and 84.5%, and the 3-year DFS rates of the experimental group (IMV high ligation and left colonic artery D3 lymph node preservation group) in this study were estimated to be 85% [12, 13]. The 3-year DFS rates of patients with low IMA ligation and 253 lymphadenectomy were 72.4% and 83.9%, respectively, and the 3-year DFS rate of the control group (IMV low ligation and left colonic artery D3 node dissection group) was estimated to be 78% [12, 13]. Assuming 3-year DFS rates of 85% (high ligation) and 78% (low ligation), a superiority margin (hazard ratio) of 0.90, *α* = 0.05, *β* = 0.8, and a superiority cutoff value of the risk ratio of 0.90, the calculation was performed by using a two-sided *α* (0.05), and the enrollment time was 2 years according to the ratio of 1:1 between the two groups, assuming that the unit enrollment rate was equal when patients were recruited and that the follow-up time was 3 years. PASS 15.0 software was used for calculations and the loss-to-follow-up rate of both groups was set at 20%; thus, 758 cases are required for each group. The total required sample size is 1,516.

### Patient enrollment process

#### Perioperative management

Bowel preparation: The usual bowel preparation for 1–2 days should be followed.

Antibiotics: Broad-spectrum antibiotics for gram-negative and gram-positive bacteria should be given intravenously before surgery. After the operation, the diet should be gradually resumed according to the patient’s condition. An abdominal drainage tube should be placed during the operation and the extraction time should be determined according to the drainage volume.

#### Preoperative evaluation

Electronic colonoscopy and pathological biopsy confirm the diagnosis; lung computed tomography (CT), abdominal non-contrast and contrast-enhanced CT, and pelvic or rectal MRI (with or without positron emission tomography [PET]-MRI) can be used to preliminarily determine the depth of tumor invasion in the intestinal wall, the metastasis of regional lymph nodes, and the clinical stage of the tumor. Blood tumor markers: carcinoma embryonic antigen and CA19–9. If necessary, CT angiography can be performed to evaluate the presence of the arc of Riolan, abdominal MRI, liver contrast ultrasound, whole-body bone scan, PET-MRI, and other examinations to confirm distant metastases.

### Patient benefits

All enrolled patients will be prioritized and can voluntarily withdraw at any time.

### Major surgical steps

Low-ligation group: IMV ligation at the left colonic artery bifurcation with D3 lymphadenectomy.

#### Step I: Laparoscopic exploration

The patient’s head is low, the feet are high, and the conventional five-hole method is used to establish the pneumoperitoneum and comprehensively explore the abdominopelvic cavity. The abdominopelvic cavity is checked for metastases, adhesions, ascites, and enlarged lymph nodes, among others.

#### Step II: Identification of ureters and dissection of submesenteric arteries and veins

The peritoneum at the junction of the sigmoid colon and rectum is incised, with careful ureter identification and protection. The mesentery of the sigmoid colon is mobilized to the place to be resected and concurrently downstream from the upper rectum and the upper rectum from the mesangium. The left colonic artery is free and preserved, and the left colonic artery is ligated and severed after branching out of the inferior mesenteric artery. The lymph nodes at station 253 are dissected (the origin of the inferior mesenteric artery is the cephalad border, the medial border of the IMV is the lateral border, the left semicolonic artery is the foot border, and the right side of the inferior mesenteric artery is the medial border), and ligation and dissection are performed at the intersection of the IMV and the left colonic artery.

#### Step III: Separation of the rectum

Downstream along the presacral space to the coccyx, both sides of the rectum are freed, the lateral ligaments on both sides of the rectum are removed, the anterior wall of the rectum and the rectum to 2 cm below the tumor are freed with exposure of the intestinal wall, and the rectum is cut off and closed with straight cutting closure.

#### Step IV: Digestive tract reconstruction

A mini-laparotomy is performed, creating the incision layer by layer into the abdominal cavity. The sigmoid colon and rectum are removed, and the sigmoid colon is transected by ≥10 cm proximal to the tumor. To ensure that there is no bleeding at either end of the broken ends, the broken ends of the sigmoid colon are placed with a gastrointestinal stapler against the needle seat, and the purse sutures are tightened and ligated. The pneumoperitoneum is reconstructed, the anus is fully dilated, the circular stapler is inserted transanally, the anvil post is advanced through the rectal stump, with the stapler connected against the needle seat, the stapler is tightened and fired to complete the anastomosis, the integrity of the upper and lower incision margins is checked, and the smooth and tension-free status of the anastomosis are confirmed.

